## \*\*Protocol Synopsis\*\*

| **\*\*Study Title\*\*** | Bilateral Auricular Vagus Nerve Stimulation for Promoting Motor Function Reconstruction after Stroke: A Prospective, Safety, Multicenter, Randomized Controlled Study

\_\_\_\_\_

\_\_\_\_\_

\_\_\_\_\_

\_\_\_\_\_

| **Study Objective** | This project aims to observe the therapeutic effect and safety of bilateral auricular vagus nerve electrical stimulation on motor dysfunction reconstruction after stroke, and to elucidate its brain function rehabilitation mechanism using fNIRS technology, thereby laying a theoretical foundation for the clinical application of bilateral auricular vagus nerve electrical stimulation in treating post-stroke motor dysfunction. |

| **Study Design** | Prospective, multicenter, sham-randomized controlled study |

| **Study Population** | **Inclusion Criteria:** (1) Age between 18 and 65 years; (2) Diagnosed with stroke (including ischemic stroke and hemorrhagic stroke) by a qualified clinician according to the "Chinese Stroke Prevention and Treatment Guidelines" from 2021 onwards; (3) Stroke recovery period, stable vital signs, no disease progression; (4) Presence of limb motor dysfunction, diagnosed with hemiplegia. **Exclusion Criteria:** (1) Limb motor dysfunction caused by other diseases; (2) Presence of psychiatric system diseases or cognitive dysfunction preventing cooperation with rehabilitation training and taVNS therapy; (3) Unstable vital signs; (4) Implanted cardiac pacemaker, uncontrolled epilepsy, history of vasovagal syncope, or other contraindications for taVNS. |

| **Interventions** | (1) **Conventional Treatment Group:** Based on drug therapy, provide conventional rehabilitation treatment for stroke hemiplegic motor dysfunction, including comprehensive rehabilitation such as exercise therapy, occupational therapy, physical agent therapy, conventional acupuncture, etc. (2) **Left-sided taVNS Group:** Based on the conventional treatment group, provide classic non-invasive left-sided auricular vagus nerve electrical stimulation. taVNS parameters: left ear, frequency 25Hz, pulse width 300us, current 6 mA. (3) **Bilateral taVNS Group:** Based on the conventional treatment group, provide non-invasive bilateral auricular vagus nerve electrical stimulation. taVNS parameters: both ears, frequency 25Hz, pulse width 300us, current 6 mA. |

| **Endpoint Measures** | **Primary Endpoint Evaluation Indicators:** Fugl-Meyer Assessment for Upper Extremity (FMA-UE) and Fugl-Meyer Assessment for Lower Extremity (FMA-LE). **Secondary Endpoint Evaluation Indicators:** Wolf Motor Function Test (WMFT), Balance evaluation and training system, Berg Balance Scale (BBS), Holden Functional Ambulation Classification (FAC), Modified Barthel Index (MBI), functional Near-Infrared Spectroscopy (fNIRS), functional Magnetic Resonance Imaging (fMRI). |

| **Planned Sample Size & Justification** | Sample size was determined using  $N = 2 \times \left[ \frac{(Z_{\alpha/2} + Z_{\beta})^2 \sigma^2}{d^2} \right]$  and statistical power analysis software G\*Power 3.1. Referring to the effect size observed in studies like Dawson et al. (Cohen's  $d = 0.632$ ), with  $\alpha = 0.05$  and statistical power  $(1 - \beta)$  equal to 80%, the estimated sample size per group should be 34. Considering a 10% clinical dropout rate, the sample size per group was adjusted to 38, totaling 114 participants across three groups. |

| **Statistical Analysis** | Statistical analysis will be performed using R software. For demographic and baseline characteristics, continuous variables conforming to normal distribution will be expressed as mean  $\pm$  standard deviation ( $\bar{x} \pm s$ ) and compared between groups using independent samples t-test; if not normally distributed, they will be expressed as median and interquartile range (IQR) and analyzed using Mann-Whitney U test. Categorical variables will be compared using Chi-square test or Fisher's exact test based on sample size and expected frequencies. For primary and secondary outcome measures (e.g., FMA-UE, FMA-LE, WMFT, BBS, MBI scores), Linear Mixed Effects Models (LMM) will be used to

handle repeated measures data, implemented via the "nlme" package in R, to assess changes over time and differences between groups, accounting for correlations within subjects across multiple time points. Post-hoc subgroup analyses will explore differential efficacy of taVNS across different stroke types (ischemic vs. hemorrhagic) and lesion locations. 
 For safety indicators, normality tests will first be performed on Heart Rate Variability (HRV) and blood pressure data. If normally distributed, paired sample t-tests will be used to compare values before and during treatment; if not, Wilcoxon signed-rank test will be used. Comparison of adverse event incidence rates between groups will use Chi-square test or Fisher's exact test.  $p < 0.05$  will be considered statistically significant. |

| **\*\*Study Duration\*\*** | This project is expected to be completed in 3 years (January 2025 --- December 2027). |

**\*\*Abbreviations List\*\***

| **Abbreviation** | **Definition**                            |
|-------------------------|--------------------------------------------------|
| :-----                  | :-----                                           |
| VNS                     | Vagus Nerve Stimulation                          |
| taVNS                   | Transcutaneous Auricular Vagus Nerve Stimulation |
| FMA-UE                  | Fugl-Meyer Assessment for Upper Extremity        |
| FMA-LE                  | Fugl-Meyer Assessment for Lower Extremity        |
| BBS                     | Berg Balance Scale                               |
| FAC                     | Functional Ambulation Classification             |
| MBI                     | Modified Barthel Index                           |
| fNIRS                   | functional Near-Infrared Spectroscopy            |
| fMRI                    | functional Magnetic Resonance Imaging            |

**\*\*1. Research Background\*\***

**\*\* (1) Significance of Motor Function Rehabilitation after Stroke for Promoting Healthy China Construction\*\***

According to statistics, the incidence of stroke in China is 150/100,000, ranking first in the world, and approximately 80% of stroke patients experience hemiplegia or limb motor dysfunction. Post-stroke limb motor dysfunction limits patients' life radius and range of activities, severely reduces their quality of life and sense of well-being, and places a heavy economic burden and mental pressure on families and society. Therefore, effectively promoting the recovery of motor function in stroke patients with hemiplegia and improving their quality of life hold significant social importance for advancing the "Healthy China 2030" strategy.

**\*\* (2) Motor Function Rehabilitation Methods after Stroke and Transcutaneous Auricular Vagus Nerve Stimulation\*\***

Current rehabilitation treatments for motor dysfunction in the sequela phase of stroke mainly

include exercise therapy, physical agent therapy, occupational therapy, traditional Chinese medicine treatments, and neuromodulation techniques. Neuromodulation technology has developed rapidly in the field of neuroscience over the past 20 years and has wide applications in the treatment of nervous system diseases. Neuromodulation techniques can be classified as non-invasive or invasive based on whether they involve penetration, and as peripheral or central neuromodulation techniques based on the stimulation target site. However, some neuromodulation techniques are limited in their clinical application and promotion for post-stroke motor dysfunction rehabilitation due to factors such as being invasive, having long treatment cycles, or exhibiting unclear efficacy. Therefore, exploring new neuromodulation therapies to accelerate the process of motor function reconstruction after stroke is of great importance.

Vagus nerve stimulation includes implanted vagus nerve stimulation (VNS) and non-invasive transcutaneous auricular vagus nerve stimulation (taVNS). taVNS is a non-invasive peripheral neuromodulation technique that stimulates the auricular branch of the vagus nerve to activate related brain areas and regulate central nervous system activity to achieve therapeutic effects (see Schematic Diagram 1). Currently, taVNS is primarily used to treat diseases such as refractory epilepsy, recurrent depression, cognitive function in brain injury, and chronic disorders of consciousness after brain injury. Our previous randomized controlled trial showed that continuous left-sided taVNS treatment could improve the arousal level of patients in a minimally conscious state, enhance their brain electrical activity function and evoked potential neural conduction pathways, with no related adverse reactions observed during treatment. In recent years, literature has gradually reported the application of taVNS in treating post-stroke motor dysfunction, attracting widespread academic attention.

**\*\*Figure 1 Schematic Diagram of taVNS Treatment Operation and Mechanism\*\***

**\*\*(3) Current Status and Shortcomings of taVNS in Reconstructing Stroke Motor Function\*\***

Numerous basic animal experiments and clinical trials have shown that taVNS can promote motor reconstruction after stroke and improve motor function. In 2021, Dawson et al. published a series of studies in *Lancet* and *Neurorehabilitation and Neural Repair*, using randomized double-blind clinical trials, demonstrating that implanted VNS combined with motor function training was significantly more effective than sham VNS combined with motor function training for upper limb motor function rehabilitation in ischemic stroke patients. Since then, extensive attention has been paid to the effect of non-invasive taVNS on the recovery of motor dysfunction after stroke. Bashar et al. used a clinical trial to show that closed-loop taVNS (Motor Activated Auricular Vagus Nerve Stimulation, MAAVN) could improve the upper limb Fugl-Meyer motor function score and quality of life in stroke patients. The current mechanisms of taVNS for treating post-stroke motor dysfunction mainly include: reducing neuronal apoptosis in the stroke area, reducing infarct volume, regulating neurotransmitter release, inhibiting the activation of neuroinflammatory factor-related pathways, enhancing neural circuit plasticity, and altering blood-brain barrier permeability.

However, there are still some shortcomings in VNS for treating post-stroke motor dysfunction. \*\*VNS techniques are mainly invasive implants or left-sided unilateral taVNS, the observation subjects are mainly upper limb motor dysfunction after stroke, and there is a lack of large-sample, multicenter randomized controlled trials.\*\* Furthermore, literature suggests that activating \*\*bilateral auricular vagus nerves can increase sensory input to brainstem neural pathways, enhancing the therapeutic effect of VNS, with effects superior to unilateral taVNS\*\*^[16]^ . Based on this, this project intends to use bilateral taVNS as the intervention, target upper and lower limb motor dysfunction after stroke, and conduct a prospective, multicenter, sham-randomized controlled study to clarify the clinical efficacy and safety of bilateral taVNS for treating upper and lower limb motor dysfunction after stroke, and to elucidate the brain function rehabilitation mechanism of taVNS in treating post-stroke motor dysfunction.

## **\*\*2. Study Objectives\*\***

2.1 **\*\*Primary Research Objective:\*\*** This project aims to observe the therapeutic effect of bilateral taVNS on motor dysfunction reconstruction after stroke, and to elucidate its brain function rehabilitation mechanism using fNIRS and fMRI technology, thereby laying a theoretical foundation for the clinical application of bilateral taVNS in treating post-stroke motor dysfunction.

2.2 **\*\*Secondary Research Objective:\*\*** To study the safety of unilateral taVNS in treating stroke patients.

## **\*\*3. Study Overview\*\***

**\*\*3.1 Overall Study Design:\*\*** This is a prospective, safety, multicenter, randomized controlled study.

### **\*\*3.2 Study Population\*\***

#### **\*\*3.2.1 Inclusion Criteria\*\***

- (1) Age between 18 and 65 years;
- (2) Diagnosed with stroke (including ischemic stroke and hemorrhagic stroke) by a qualified clinician according to the "Chinese Stroke Prevention and Treatment Guidelines" from 2021 onwards;
- (3) Stroke recovery period, stable vital signs, no disease progression;
- (4) Presence of limb motor dysfunction, diagnosed with hemiplegia.

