#### **\*\*3.4 Randomization\*\***

##### **\*\*3.4.1 Method for Generating Random Allocation Sequence\*\***

> Use a random number table for randomization.

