#### **\*\*3.6 Study Procedures\*\***

Study steps mainly include clinical trial randomization and grouping, follow-up and data collection at baseline (T0), at 2 weeks of treatment (T1), at the end of 4 weeks (T2), and at 8 weeks after treatment completion (T3), as detailed below:

- (1) **\*\*Randomization and Grouping:\*\*** Enroll eligible stroke patients with motor dysfunction and assign them to the Conventional Treatment Group, Left-sided taVNS Group, or Bilateral

taVNS Group using a random number table.

(2) **\*\*Collection of Basic Patient History Information:\*\*** Collect basic information for enrolled subjects, including age, gender, time since onset, stroke type, education level, marital status, etc.

(3) **\*\*Data Collection at T0, T1, T2 time points:\*\*** Fugl-Meyer Assessment for Upper Extremity (FMA-UE) and Lower Extremity (FMA-LE), Wolf Motor Function Test (WMFT), Balance evaluation and training system, Berg Balance Scale (BBS), Holden Functional Ambulation Classification (FAC), Modified Barthel Index (MBI), functional Near-Infrared Spectroscopy (fNIRS).

(4) **\*\*Data Collection at T3 follow-up time point:\*\*** Follow up via phone or outpatient visit to collect Berg Balance Scale (BBS) and Modified Barthel Index (MBI) scores at 8 weeks after treatment completion.

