### **\*\*6.2 Efficacy Analysis and Statistical Methods\*\***

Statistical analysis will be performed using R software. For demographic and baseline characteristics, continuous variables conforming to normal distribution will be expressed as mean  $\pm$  standard deviation ( $\bar{x} \pm s$ ) and compared between groups using independent samples t-test; if not normally distributed, they will be expressed as median and interquartile range (IQR) and analyzed using Mann-Whitney U test. Categorical variables will be compared using Chi-square test or Fisher's exact test based on sample size and expected frequencies.

For primary and secondary outcome measures (e.g., FMA-UE, FMA-LE, WMFT, BBS, MBI scores), Linear Mixed Effects Models (LMM) will be used to handle repeated measures data, implemented via the "nlme" package in R, to assess changes over time and differences between groups, accounting for correlations within subjects across multiple time points. Post-hoc subgroup analyses will explore differential efficacy of taVNS across different stroke types (ischemic vs. hemorrhagic) and lesion locations.

For safety indicators, normality tests will first be performed on Heart Rate Variability (HRV) and blood pressure data. If normally distributed, paired sample t-tests will be used to compare values before and during treatment; if not, Wilcoxon signed-rank test will be used. Comparison of adverse event incidence rates between groups will use Chi-square test or Fisher's exact test.  $p < 0.05$  will be considered statistically significant.

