**\*\*10. Expected Schedule and Completion Date\*\***

This project is expected to be completed in 3 years. The overall schedule and progress are as follows:

[January 2025 - June 2025]{.underline}

Prepare and refine all pre-trial tasks, explain patient inclusion and exclusion criteria, conduct standardized training for scale administration, and provide homogeneous training for taVNS treatment to achieve standardized homogeneity across the three clinical centers. Additionally, complete ethics applications and approvals at the three clinical centers, and complete registration on the Chinese Clinical Trial Registry website.

[July 2025 - June 2026]{.underline}

Begin enrolling stroke patients first in the Rehabilitation Medicine Department of the First Affiliated Hospital of Nanchang University, administer taVNS treatment, monitor safety, and perform assessments including FMA-UE, FMA-LE, WMFT, Balance evaluation and training system, BBS, FAC, MBI, and fNIRS.

[July 2026 - December 2027]

Simultaneously initiate trial enrollment in the Rehabilitation Medicine Departments of The Rehabilitation Hospital Affiliated to Nanchang University and The First Affiliated Hospital of Gannan Medical University, administer taVNS treatment, monitor safety, and perform assessments including FMA-UE, FMA-LE, WMFT, Balance evaluation and training system, BBS, FAC, MBI, and fNIRS.

[December 2027 - June 2028]

Conduct supplementary clinical trials, data collection and processing, statistical analysis of experimental data, manuscript writing, and final reporting.

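### Time since onset is collected but left out of the randomisation, efficacy model and subgroups, although eligibility sets no range for it; the main cost is lost precision

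*Protocol*

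**What the plan says.** - **Eligibility (Protocol 3.2.1, item 3; same in the synopsis).** The phase criterion is "Stroke recovery period, stable vital signs, no disease progression". No minimum or maximum time since onset is given, the term is not defined, and no exclusion criterion in 3.2.2 limits it.
- **Background (section 1, part 2).** A general sentence on existing therapies uses another term: "Current rehabilitation treatments for motor dysfunction in the sequela phase of stroke mainly".
- **Data collected (3.6, item 2).** Basic history is recorded, "including age, gender, time since onset, stroke type, education level, marital status, etc". The protocol mentions time since onset nowhere else.
- **Randomisation (3.4.1).** "Use a random number table for randomization". Section 3.4.2 adds that randomisation is central. No stratification factor is named.
- **Efficacy analysis (6.2).** FMA-UE and FMA-LE go into a linear mixed model for change over time and group differences; no baseline covariate is named. For subgroups: "Post-hoc subgroup analyses will explore differential efficacy of taVNS across different stroke types (ischemic vs. hemorrhagic) and lesion locations".
- **Visits (3.6).** Both FMA scales are measured at baseline, 2 weeks and 4 weeks. The later follow-up collects only BBS and MBI.

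**The concern.** All three arms receive conventional rehabilitation, and the taVNS effect is judged against whatever recovery happens anyway over 4 weeks. If patients enter at different points of recovery, their expected FMA change under conventional care differs for reasons unrelated to treatment. That motor recovery is faster early than late is assumed here as general clinical knowledge; the protocol does not state it.

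A mixed model with group and visit handles correlation within a patient. It does not explain why one patient's score climbs and another's stays flat, so that spread remains in the error term. The baseline FMA cannot fully stand in for phase, because the same score can belong to a patient still recovering or to one who has plateaued.

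Two things are at stake: precision in the primary comparisons, and the ability to correct a chance difference between arms in time since onset. The variable needed for both is already collected.

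**Working it through.** **The plan's own figures.** The plan gives no figure for time since onset. Its nearest figure is the sample size in 6.1: 34 per group, raised to 38 for 10% dropout (34/0.9 = 37.8) and 114 in total (3 × 38). The dropout step reproduces. The 34 does not follow from the printed formula: 2 × (1.960 + 0.842)²/0.632² = 39.3, so 40 per group. That is a separate matter, and nothing below depends on it except the power illustration in step 4.

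**Assumed inputs (none is in the documents).** Half the patients early and half late; SD of the 4-week FMA-UE change 6 points early and 4 points late; mean natural gain differing by d = 3, 5 or 7 points.

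**1. Share of change variance due to phase.** Within-phase variance = (6² + 4²)/2 = (36 + 16)/2 = 26. Between-phase variance for a half-and-half split = (d/2)². Gain in effective sample from full adjustment = total/within.

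| d | Between | Total | Share | Gain |
|---|---|---|---|---|
| 3 | 2.25 | 28.25 | 8.0% | 28.25/26 = 1.09 |
| 5 | 6.25 | 32.25 | 19.4% | 32.25/26 = 1.24 |
| 7 | 12.25 | 38.25 | 32.0% | 38.25/26 = 1.47 |

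**2. Sensitivity to the split.** With early share p, within = 36p + 16(1 − p) and between = p(1 − p)d². At p = 0.2 the gain for d = 3 to 7 is 1.07 to 1.39; at p = 0.8 it is 1.05 to 1.25. A population mostly in one phase gains less.

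**3. Chance imbalance.** For two arms of 38 and p = 0.5, the SD of the difference in early share is √(2 × 0.25/38) = 0.115. The probability of a difference of 15 percentage points or more is about 19% by the normal approximation (about 21% by exact binomial). At that imbalance the arm difference shifts by 0.15 × 3 = 0.45 to 0.15 × 7 = 1.05 points. The standard error of an arm difference is √28.25 × √(2/38) = 1.22 points for d = 3, and √38.25 × √(2/38) = 1.42 points for d = 7. The shift is therefore 0.45/1.22 = 0.4 to 1.05/1.42 = 0.7 standard errors.

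**4. What adjustment could do for power.** With 34 evaluable per group, two-sided α = 0.05 and Cohen's d = 0.632, power = Φ(0.632 × √(34/2) − 1.96) = Φ(0.65) = 74%. If time since onset explains a share R² of the variance, the effect divided by the residual SD becomes 0.632/√(1 − R²). Power is then 78%, 83% or 88% for R² = 10%, 20% or 30%. This takes 0.632 as standardised on an SD that includes the phase spread, which the documents do not settle.

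**The case against.** **A covariate and a subgroup factor belong in the SAP.** Often they do, and a separate SAP may exist. But section 6 of this protocol is itself titled as the statistical analysis plan and states the model and the subgroup factors. The point proposes a more precise version of that stated model. A further exploratory subgroup split of 114 patients in three arms would add little, and none is proposed.

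**The magnitudes are assumed.** This stands. The split, the SDs and the gap have no source in the documents, and a narrow meaning of recovery period would shrink every figure. The gains also assume that true phase is known; log time since onset would generally recover less.

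**Broad entry may be deliberate.** It may, for recruitment or generalisability. Adjustment leaves that choice intact.

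Four stronger readings are tempting, and the documents do not support them:
- *The trial enrols patients years after stroke.* A reader might take "from 2021 onwards" as dating the diagnosis and, with the last enrolment window "July 2026 - December 2027", arrive at strokes almost 7 years old. The phrase follows the guideline title and reads more naturally as the guideline version. A wide mix is permitted by the missing limits; it is not stated.
- *The background sets a contradictory target phase.* The sequela-phase sentence is general background. Section 1, part 3 states the target as limb motor dysfunction after stroke, without a phase. The wording needs aligning, but it is not a conflict between eligibility rules.
- *The variable is used nowhere.* Section 6.2 compares baseline characteristics between groups, which would probably include it. That comparison does not adjust the treatment effect.
- *Imbalance biases the trial.* Under randomisation an imbalance arises by chance and is already covered by the standard error and the type I error rate.

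**Conclusion.** The point holds as one of efficiency and clarity. Eligibility leaves time since onset unbounded in writing, the variable is collected, and the stated randomisation, efficacy model and subgroups do not use it. The surer cost is lost precision in the 4-week FMA-UE and FMA-LE comparisons. Chance imbalance is a secondary cost, under one standard error even at a 15-point difference in early share.

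Under the stated assumptions adjustment is worth up to about 9% to 47% more effective sample. That range indicates what might be gained and does not estimate what this trial will lose: it rests on an assumed half-and-half mix, assumed SDs and gaps, and perfect capture of phase. The unadjusted analysis would still be valid. The change is worth making because the data are already planned and it costs almost nothing.

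**What to change.** **Main change (section 6.2).** Prespecify log time since onset, and its interaction with visit, as fixed covariates in the FMA-UE and FMA-LE mixed models, and fix this before any outcome data are seen by arm. The interaction is essential: a main effect alone shifts a patient's level at all visits, whereas differing natural recovery appears as differing change between visits. With three FMA visits treated as categories this costs three degrees of freedom per model (one for the main effect, two for the interaction). It needs no new data and no extra patients.

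**Separate clarification (section 3.2.1, item 3).** The investigators should state what the recovery period means as a range of time since onset of their own choosing, so that the three centres apply the criterion alike, and reconcile it with the sequela-phase wording in section 1. This is a wording change; depending on the range chosen, it may exclude some patients who could otherwise have entered. The main change does not depend on it.
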